### Sample size

With regards to our primary research aim, we will test the hypothesis that the intervention condition will result in a significantly higher rate of detected cases of DVA compared to the control condition over a 12 month follow up period.

To calculate the sample size needed in this cluster RCT, we started with a sample size calculation assuming individual randomization and inflated this number by a design effect to account for randomization by cluster [36]. This inflation factor (IF) is dependent on average cluster size, and the intra-class correlation (ICC). Using this calculation we found that with a minimum of 12 intervention teams and 12 control teams, with the assumption of a detection rate of 0.25% in control teams (based on the LARA study [13]) and an ICC of 0.03 (based the IRIS study [30]) we will be able to detect a three- to four-fold increase (Beta = 3.55) in the detection rate with a power of 80% and a significance level of 0.05. This calculation assumes an average of 200 patients in every team.

Regarding knowledge and attitudes on DVA, a sample size of 24 teams allows us to detect a large sized increase of knowledge between the intervention and control teams.

In order to answer Aim 2 we will ask a purposeful sample of persons from every profession involved in the study for an in depth interview about the feasibility, sustainability and acceptance of the intervention. A minimum of ten interviewees will be selected from the DVA services, and ten from CMH services. Furthermore all trainers in this study will be interviewed on their experiences. Additionally, we will interview a total of 30 patients or more until saturation of the themes is achieved.

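### The stated 80% power for a 3.55-fold increase does not follow from the stated inputs: with the design effect applied, power is about 20%

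*Protocol article*

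**What the plan says.** The Sample size section of the protocol article gives both the method and all the inputs. The authors started from a sample size for individual randomisation and multiplied it by an inflation factor that depends on average cluster size and ICC. The inputs are:

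- clusters: "with a minimum of 12 intervention teams and 12 control teams";
- control rate: "the assumption of a detection rate of 0.25% in control teams", attributed to an earlier pilot study in mental health services;
- ICC: 0.03, attributed to an earlier cluster trial in primary care;
- cluster size: "This calculation assumes an average of 200 patients in every team".

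Testing at the 0.05 level, the authors conclude: "we will be able to detect a three- to four-fold increase (Beta = 3.55) in the detection rate with a power of 80" per cent. Whether the test is one- or two-sided is not stated. This is the only power statement for the primary outcome.

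**The concern.** A cluster size of 200 with an ICC of 0.03 implies a design effect of nearly 7, and a control rate of 0.25% implies very few events. A ratio of 3.55 looks too small to be detectable with 80% power under both conditions at once.

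The label adds to the doubt. Beta normally denotes the type II error or a regression coefficient. Read as a log coefficient, 3.55 would be a ratio of exp(3.55) = 34.8, which contradicts the three- to four-fold wording beside it. It can only be a rate ratio.

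If the power is far below 80%, a null result could be taken as evidence against a three- to four-fold effect that the design could not reliably detect. At the stated rate, sparse counts could also prevent the planned model from estimating a rate ratio.

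**Working it through.** **Inputs** (all from Sample size): p1 = 0.0025; ratio 3.55, so p2 = 0.008875 and the difference is 0.006375; k = 12 teams per arm; m = 200, so 2,400 patients per arm; ICC = 0.03; alpha = 0.05, taken as two-sided with one-sided also tried.

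**1. Trying to reproduce the stated figure without inflation.** With n = 2,400 per arm, the sum of the variances is 0.0025 × 0.9975 + 0.008875 × 0.991125 = 0.01129.

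- SE = √(0.01129/2400) = 0.002169
- z = 0.006375/0.002169 = 2.94
- power = Φ(2.94 − 1.96) = 83.6%

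The ratio detectable with 80% power is 3.26 (arcsine), 3.39 (z test), 3.54 (t with 22 df), 3.62 (continuity-corrected) or 3.63 (log ratio). The stated 3.55 lies within this range.

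**2. Applying the method the section describes.**

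- Design effect = 1 + (200 − 1) × 0.03 = 6.97
- Effective n = 2400/6.97 = 344.3 per arm
- SE = √(0.01129/344.3) = 0.00573
- z = 0.006375/0.00573 = 1.11
- power = Φ(1.11 − 1.96) = 19.9%

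Other choices at the same ratio:

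| Variant | Power at 3.55-fold |
|---|---|
| Pooled z, two-sided | 19.8% |
| Arcsine, two-sided | 21.3% |
| Log ratio, two-sided | 17.9% |
| t with 22 df, two-sided | 18.5% |
| Beta-binomial simulation (ICC 0.03), t test on team proportions | 18.6% |
| Pooled z, 250 patients per team | 20.3% |
| Pooled z, one-sided | 29.7% |
| Arcsine, one-sided | 31.5% |

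**3. Ratio detectable with 80% power, inflation applied.** It is 11.6 by the z test. Check: p2 = 11.6 × 0.0025 = 0.029; SE = √((0.002494 + 0.028159)/344.3) = 0.00944; z = 0.0265/0.00944 = 2.81; power = Φ(0.85) = 80%. Other two-sided results are 9.75 (arcsine), 12.4 (t with 22 df) and about 22 (log ratio). In the simulation, power is 82% at 10-fold.

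**4. Sample size by the same method.** At 3.55-fold, individual randomisation needs 2,184 per arm (pooled z). Inflated, that is 2,184 × 6.97 = 15,222 per arm, or 15,222/200 = about 76 teams per arm instead of 12.

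**5. What would make 3.55 right with inflation applied.**

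- A different control rate: at 1.5% (p2 = 5.325%), power is 79% by the z test, so a rate near 1.5% is needed, six times the stated one.
- A different ICC: the design effect could be at most 2400/2184 = 1.099, so ICC = 0.099/199 = 0.0005, one-sixtieth of the stated one.

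**6. Event counts at the stated rate.** Expected control detections are 2,400 × 0.0025 = 6, or 0.5 per team. Under a beta-binomial with ICC 0.03, a control team has zero detections with probability 0.85. All 12 do with probability 0.146 (about 0.85 to the power 12), and the rate ratio then has no finite estimate.

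**The case against.** The arithmetic itself has no good defence. Larger teams, one-sided testing or reading 3.55 as a log coefficient do not bring the power near 80%. The fair objections concern how far one may go beyond it.

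- **Cause.** The article does not reveal which figure slipped. Leaving out the inflation fits well, but so would a misprinted control rate or ICC. This stands: the conclusion should be that the inputs and the result conflict, not that one particular error was made.
- **Detectable ratio.** The range of 10- to 12-fold depends on the scale; a log-ratio formula gives about 22. This also stands, but it makes 10- to 12-fold the favourable end.
- **Planned analysis.** Simulated power for a team-level Poisson GEE runs somewhat higher, about 25% to 32%. With 12 teams per arm and an uncorrected robust variance, however, type I error was about 10% among estimable runs, so that figure flatters the design. Adjustment for baseline detections (Statistical methods) could raise power, but it is a subsequent analysis and not part of the stated calculation.
- **Sparse counts.** The six expected control detections and the 15% chance of none hold only if 0.25% is right. The abstract defines the outcome to include any history of abuse, so the true rate may be higher.
- **Acknowledgement.** The Discussion concedes that a cluster trial may miss a true effect and that 24 clusters is few. That general caution does not correct the 80% figure.

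**Conclusion.** The concern holds. Under the stated control rate, ICC, team size and number of teams, two-sided power for a 3.55-fold increase is about 20% (18% to 21% by the usual large-sample formulas), and at most about 32% one-sided. An 80% power needs roughly a 10- to 12-fold increase, from 0.25% to about 2.4% to 2.9%, and more on the log scale. The result assumes equal team sizes, the standard design effect and no gain from baseline adjustment, which is the calculation the section describes. No formula tried brings power near 80% with the inflation applied. Which input is wrong cannot be settled from the article. This must be fixed, because it is the only basis given for the size of the trial on its primary outcome.

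**What to change.** Reconcile the control rate, the ICC and the inflation step in the Sample size section, and state which figure was wrong.

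- If 0.25% and 0.03 stand, say that 12 teams of 200 per arm give about 20% power for a 3.55-fold increase, and that 80% power is reached at about a 10- to 12-fold increase. Name the formula and whether the test is two-sided.
- If the control rate or the ICC is the error, give the corrected value and the detectable ratio that follows from it.
- In either case call the figure a rate ratio, not Beta.

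Before any follow-up data are opened, estimate the control rate and ICC from the 12 months of historical files that the eligibility criteria already require, and publish the detectable ratio from those estimates.

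The cost is a corrected paragraph and the search applied to baseline files. Because the keyword search has to be piloted and each case validated, this is real work, but the baseline-adjusted analysis already needs those counts. No teams are added. The price is a less favourable power statement if the stated inputs stand.

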### Recruitment

The CMH teams eligible for inclusion will be appointed by the management of the participating facilities to participate in the trail.

Recruitment regarding the in-depth interviews on feasibility, sustainability and acceptability will be done by the research team. All professionals participating in the study will be asked if they want to participate in an interview. Patients will be approached through their primary clinician at the CMH team. If a patient is interested they can contact the research team for further information and possible participation. Additionally we will recruit patients through patient support organizations, support groups for victims of DVA, and advertisements placed at the locations of the CMH services. Interested patients will be provided with an information letter on the study. After signing informed consent the patient will approached for an interview. We will interview patients until saturation of the themes is achieved. Patients will receive a fee of 20 euros after the interview.

### Randomization and blinding

We will randomly allocate the 24 CMH teams in a 1:1 allocation ratio to receive either no intervention or the BRAVE intervention. Randomization will be conducted using a web-based computer-generated randomization schedule ten-ALEA (randomization software programme, version 2.2), using block sizes of 2. Social-economic status of the service area of the CMH team dichotomized into high and low social-economic status, will be used as stratification factor. Allocation will be facilitated by an independent researcher. Due to the nature of this intervention, it is not possible to blind the CMH professionals of the teams for allocation status. An independent researcher, blinded for allocation, will be responsible for extracting the primary data fields regarding the primary outcome measure (e.g. the number of screened DVA cases per team) from the electronic patient files.

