## Methods

### Domestic violence and abuse services in context of the public health system in the Netherlands

In the Netherlands, domestic violence and abuse (DVA) services are part of the public health system. The public health system is financed by government, and services are free of charge for every citizen. The public health services cover a wide range of problems, such as domestic violence, youth work, and housing. Public health services are the responsibility of the municipality. With regards to DVA, starting from 2015, every municipality in the Netherlands has installed a helpline service, for both professionals and victims of DVA, named Veilig Thuis (Safe Home).

A Veilig Thuis-service functions as a gatekeeper. They assess cases of (suspected) DVA, provide advice in cases of (suspected) DVA and coordinate referrals to third party services on DVA. Veilig Thuis (VT) covers both child abuse and intimate partner violence.

All municipal VT-services adhere to national DVA guidelines (diagnostic and referral guidelines). These guidelines are general in nature, which means that slight differences in interpretation and execution may exist between municipalities.

Thus, the municipal care for victims of DVA offers the following services [32].

Informal advice:Assessment: if a person calls the helpline, VT will assess the situation during that phone conversation. The helpline service is available for everyone with a concern regarding DVA. This could be, for example, a co-worker, victim of DVA or a clinician.Advice: after assessment VT will offer advice to whomever using the helpline. This advice ranges from passively monitoring the situation to notifying the police because of a (potentially) dangerous situation. VT can also give referral advice.

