### Study setting

The study will be conducted in the municipalities of Rotterdam and The Hague, the Netherlands. DVA services provided in these municipalities are provided by VT Rotterdam and VT The Hague (see previous paragraph for details). Mental health care in these municipalities is provided by two big community mental health clinics (CMH) i.e. BAVO Europoort (Rotterdam) and Parnassia The Hague. These clinics provide both out-patient and in-patient mental health care and cover the Rotterdam- Rijnmond and the Hague area, which inhabits approximately 2.5 million people. Service use is free of charge for all citizens with health insurance, which is obligatory in the Netherlands, after paying a limited contribution with a maximum of 385 euros per year.

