### Intervention

The intervention consists of 1) knowledge and skills training for mental health professionals of the CMH teams about DVA, 2) knowledge and skills training of DVA practitioners about mental illness, 3) the provision and implementation of a direct care pathway between CMH services and DVA services for victims of DVA with mental illness.
*Knowledge and skills training for mental health professionals about DVA:*

The training for the teams has been developed by the research team and is aimed at improving knowledge and skills regarding detection and management of DVA. At the start of the trial, all CMH teams in the intervention group will receive a training of approximately 8 hour in total, divided over 2 days. The topics covered in the training used in the LARA-intervention were included here [13] and consist of four main themes namely;Improving knowledge about DVA; (the definition and different forms of DVA; prevalence and incidence of DVA in the Netherlands; and symptoms and signals of DVA, including cultural differences in expression).Identifying and documentation of DVA when taking the patient’s history: this theme will cover different techniques a clinician can use to discuss and assess DVA with a patient and includes advice on how to document DVA.Safety: this theme entails safety assessment and management for patients and clinicians and will also include laws and legislation on DVA in the Netherlands.Treatment/follow up: this theme will discuss referral pathways and ways to empower/support patients who are victims of DVA.The training is modified according to the characteristics of the specific municipality. This means that the teams will receive training with a referral pathway adapted to the Rotterdam and The Hague municipality, respectively.

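### Randomisation is stratified on SES alone, so the two institutions (one per city) whose patient files supply the primary outcome can be unevenly split between arms by chance and shift the realised estimate

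*Protocol article*

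**What the plan says.** All quotes are from the protocol article.

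- *Randomization and blinding*: "We will randomly allocate the 24 CMH teams in a 1:1 allocation ratio to receive either no intervention or the BRAVE intervention", "using block sizes of 2". One stratification factor is given: "Social-economic status of the service area of the CMH team dichotomized into high and low social-economic status, will be used as stratification factor".
- *Study setting*: care is provided by "two big community mental health clinics (CMH) i.e. BAVO Europoort (Rotterdam) and Parnassia The Hague", so city and institution coincide. Each city also has its own domestic violence service: "DVA services provided in these municipalities are provided by VT Rotterdam and VT The Hague".
- *Intervention*: "the teams will receive training with a referral pathway adapted to the Rotterdam and The Hague municipality, respectively".
- *Domestic violence and abuse services in context of the public health system in the Netherlands*: these services share national guidelines, but "slight differences in interpretation and execution may exist between municipalities".
- *Primary outcome*: detected cases come from a keyword search of the electronic patient files at the participating institutions. Control and intervention teams are paired there, but only so that data are extracted at the same time. This is not matching on city.
- *Statistical methods*: the main comparison uses patient numbers as denominator and accounts for team. A subsequent analysis adjusts for detected cases at baseline. City and institution are not mentioned.
- *Discussion*: with only 24 clusters, the authors accept that the arms may end up different.

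**The concern.** The outcome is what clinicians write down, retrieved by a search of each institution's files. A difference between institutions in recording habits or file structure would therefore feed straight into the measured detection rate, in both arms. Institution is fully aligned with city, it is known for every team before allocation, and it has only two levels. It is an easy grouping to balance, and the stated rule leaves it to chance.

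If one city supplies noticeably more intervention teams than control teams, part of any difference between cities appears as intervention effect, or hides it. The *Discussion* also foresees institutions reorganising teams and municipalities reorganising domestic violence services during the study. Such events could affect one city only, and a baseline count would not capture them.

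**Working it through.** The article gives no figure for city balance, so there is nothing to reproduce. The check has three parts.

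**Inputs from the article:** 24 teams, 12 per arm, blocks of 2, SES as the only stratum (*Randomization and blinding*); control detection rate 0.25%, ICC 0.03, target ratio 3.55 (*Sample size*).

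**Assumptions not in the article:** 12 teams per city, teams of equal size, city unrelated to the SES stratum, city order random within the sequence, and a city ratio r in recorded detection of 1.5 to 3.

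**1. How often is the split uneven?** Let X be the number of the 12 teams from one city that fall in the intervention arm. Then P(X = k) = C(12,k)² / C(24,12), with C(24,12) = 2,704,156.

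- P(X = 6) = 924² / 2,704,156 = 0.316
- P(X = 7) = P(X = 5) = 792² / 2,704,156 = 0.232
- P(8:4 or worse, either direction) = 1 − 0.316 − 2 × 0.232 = 0.220, or about 11% in each direction
- P(9:3 or worse) = 0.039

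A simulation of blocks of 2 with random city order gives 21.9% and 3.9%. With 10 and 14 teams per city, departures of at least 2 or at least 3 teams from an even split occur in 21% and 3.6% of allocations. With 8 and 16 teams the figures are 19% and 2.7%. The result hardly depends on the city split.

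It does depend on the order of teams. If teams were listed by institution within each SES stratum, at most one block per stratum would mix cities. With even-sized strata and 12 teams per city, at least 10 of a city's teams then sit in single-city blocks and divide 5:5, so the worst result is 7:5. The article does not state the order.

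**2. What would an uneven split do to the estimate?** With no intervention effect and city ratio r, the expected crude rate ratio is:

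- 8:4 split: (8r + 4) / (4r + 8)
- 9:3 split: (9r + 3) / (3r + 9)

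| r (assumed) | 8:4 | 9:3 |
|---|---|---|
| 1.5 | 16/14 = 1.14 | 16.5/13.5 = 1.22 |
| 2 | 20/16 = 1.25 | 21/15 = 1.40 |
| 3 | 28/20 = 1.40 | 30/18 = 1.67 |

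If the imbalance runs the other way, the reciprocals apply.

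**3. Would controlling for city gain precision?** On the plan's own inputs, the squared between-team coefficient of variation is ICC × (1 − p)/p = 0.03 × 0.9975/0.0025 = 12.0. Two equal groups with rates in ratio r contribute ((r − 1)/(r + 1))².

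- r = 2: (1/3)² = 0.11, about 1% of 12.0
- r = 3: (1/2)² = 0.25, about 2% of 12.0

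The gain in precision is negligible under those inputs. The case for the change rests on parts 1 and 2.

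**The case against.** There is a good deal to be said on the other side.

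- **Randomisation protects against bias on average, and the interval allows for chance imbalance.** This stands. A reader might infer that the design is biased; it is not. What remains is distortion conditional on an uneven allocation that could have been prevented cheaply.
- **Most of the city differences are not confounders.** This stands too. A reader might infer that the city-specific training and referral pathway confound the comparison. They are delivered to intervention teams only, so they determine which city's version weighs more in the average effect. Referral also comes mainly after detection, which is the outcome. The domestic violence services follow shared guidelines, and the article calls the differences slight. The route that survives is the institution and its records.
- **No difference between institutions is documented.** Correct. Both work with the same team model, the same eligibility rules and the same legal reporting protocol. The range for r is an assumption.
- **Baseline adjustment deals with it.** In part. Eligible teams must have 12 months of historical data, and a stable city difference would largely be absorbed. But the adjustment is placed in the subsequent analysis, and it cannot remove changes that hit one city during follow-up.
- **The missing city term may be in the full plan.** This stands. A condensed article need not list every covariate, and its sensitivity analyses are given as examples only. The absence of city from the model is therefore not an error in itself. The stratification rule, by contrast, is stated outright.
- **SES is a legitimate choice of stratifier.** Agreed. The suggestion is to add city, not to replace SES.

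**Conclusion.** The point holds as a cheap improvement to a stated design rule, not as an error that undermines the trial. With SES as the only stratifier, a city split of 8:4 or worse has a probability of about 22% (12 teams per city, random city order; less if teams are listed by institution). Under an assumed 1.5- to 3-fold city difference in recorded detection, an 8:4 split would shift the crude rate ratio by a factor of 1.14 to 1.40. A 9:3 split or worse, at about 4%, would shift it by at least 1.22 to 1.67.

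These shifts are modest beside the 3.55-fold effect the trial is sized for, and they matter more if the true effect is smaller. The documents do not support a claim of systematic bias, of confounding by training version or referral pathway, or of a worthwhile gain in precision.

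**What to change.** - **If allocation is still open:** stratify on city by SES, four strata, keeping blocks of 2. Each stratum then has at most one unpaired team, so a city of 12 teams can be split no worse than 7:5. Cost: a setting in the randomisation programme. Exact 12:12 allocation is no longer guaranteed. If all four strata are odd-sized and every unpaired team falls the same way, the arms could be 14:10.
- **If allocation is done:** report the city split by arm, and pre-specify city and the SES stratum as fixed effects in the primary model, alongside baseline detection. City and SES cost two of the roughly 22 degrees of freedom left by 24 teams and two arms. On the plan's own inputs, cases are few: 12 × 200 × 0.0025 = 6 in the control arm, and 6 × 3.55 ≈ 21 in the intervention arm if the target effect is met. The plan should therefore state in advance what happens if the adjusted model cannot be fitted.

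If the full protocol or analysis plan already includes city in the primary model, the second step is met and only the wording of the article needs to follow.
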